**Fig. 1 Fig1:**
[figure not shown]
Flowchart of participants

### Sample size

To determine the sample size, the effect sizes found in the literature have been considered. An RCT using the UP in a traditional face-to-face approach [33] obtained effect sizes of 0.56 for anxiety, measured with the BAI, and 1.11 for depression, measured with BDI-II. The mean effect size indicated in a recent meta-analysis [39] comparing transdiagnostic computerized cognitive-behavior therapy (CBT) to waitlist control was g = .93 for anxiety and g = .88 for depression.

Adopting a more conservative approach than those of the aforementioned studies, we assumed an effect size of 0.5 (Hedges’ g), which, following Cohen [62], can be considered an effect size of medium magnitude. As our design included three experimental conditions (*TIBP*, *TIBP + PA*, *WL*), a between-groups one-way ANOVA was assumed for the statistical analyses. Therefore, calculations of the necessary sample size cannot be based on Hedges’ *g* index for effect size, but rather on the *f* index [62]. Following Cohen [62], *f* = 0.25 represents an effect size of medium magnitude (and equivalent to *g* = 0.5). Thus, considering an alpha of .05 and a statistical power of .80, the total sample size required to warrant these conditions contains 159 participants (53 participants per group). To control the maximum possible loss of subjects during treatment, based on the literature about Internet-based treatments, a 30% dropout rate is expected [53, 63]. Thus, the required sample size should have 207 participants in all (69 participants per group). These calculations were accomplished with the software program *G*Power 3.1* [64].

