We intend to study the effect of both treatments in terms of efficacy for depressive and anxious symptomatology. Moreover, we aim to assess the effects of the specific treatment component designed for up-regulating PA. Finally, the effectiveness of the Internet-based program developed to apply the treatment protocol over the Internet with minimal support by the clinician will be studied. We hypothesize that: a) both self-applied protocol modalities (*TIBP* and *TIBP + PA*) will be more effective than the waiting list control condition in the treatment of ED; b) both interventions will result in significant improvements in depressive and anxious symptomatology at post- treatment, and these results will be maintained at 3- and 12- month follow-ups; c) the *TIBP + PA* will significantly outperform the *TIBP* group on PA measures; and d) both protocols will be well accepted, with no statistical differences between conditions. In this article, we present the study protocol.

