### Data analyses

Intention-to -treat analyses and per protocol analyses will be performed, and CONSORT recommendations will be followed [98]. First, the three groups will be compared to verify that there are no significant differences among them at baseline on the outcome measures in order to confirm that they are comparable after randomization. One-way ANOVAs for continuous variables and Chi-squared tests of independence for categorical ones will be used. For the continuous outcome measures on the posttest, the homoscedasticity assumption will be assessed with the Levene test. Where this assumption is met, the usual *F*-test will be applied to compare the posttest means for the three experimental conditions. If the homoscedasticity assumption is not met, the Brown-Forsythe *F*-test will be applied. Statistically significant *F*-tests will be followed by post hoc comparisons. In particular, the Tukey procedure will be applied where the homoscedasticity assumption is met, and the Games-Howell procedure if this assumption is not met.

The intention-to-treat principle will be used when analyzing primary and secondary post-treatment data and data collected at the 3- and 12-month follow-ups, using mixed-effect models with full information maximum likelihood estimation. This method has been recommended due to its flexibility on repeated-measures ANOVAs in handling missing data more appropriately [99]. To complement the results of the ANOVAs and post hoc comparisons, effect sizes will be calculated by using the standardized mean difference proposed by Cohen [62]. These effect sizes will be calculated to assess both within- and between-group changes, all of them based on a pooled standard deviation.

Although per protocol analyses (completers only analysis) suffer from selection bias, they will also be conducted to help to draw conclusions about the maximum treatment efficacy in patients who comply fully with the treatment [100].

When the trial ends, the analytic methodology for the RCT will be reviewed before analyzing the data in order to select the most appropriate analytic procedures.

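### f = 0.25 is not equivalent to g = 0.5 with three arms, and the stated 80% power belongs to the omnibus F-test, not to the pairwise comparisons that decide hypotheses (a) and (c)

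*Protocol article*

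**What the plan says.** The Sample size section of the protocol article starts on the pairwise scale: "we assumed an effect size of 0.5", expressed as Hedges' g. Because there are three conditions, "a between-groups one-way ANOVA was assumed for the statistical analyses", and the effect is moved to Cohen's f with the statement that f = 0.25 "represents an effect size of medium magnitude (and equivalent to" g = 0.5. Then, "considering an alpha of .05 and a statistical power of .80", the required total "contains 159 participants (53 participants per group"). This is raised to 207 (69 per group) for an expected 30% dropout.

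The hypotheses are at the end of the Introduction. Hypothesis (a) is that both protocols "will be more effective than the waiting list control condition in the treatment of ED". Hypothesis (c) is that TIBP + PA outperforms TIBP on positive affect measures. The Data analyses section compares pairs only after a significant F: "In particular, the Tukey procedure will be applied where the homoscedasticity assumption is met", and Games-Howell otherwise. No power is given for any pairwise comparison.

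**The concern.** Two things do not fit together.

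First, the section says that g cannot be used because there are three conditions, and then uses the two-group conversion f = d/2. The two values share Cohen's label of medium, but they do not describe the same effect in this design.

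Second, the 80% is the probability that an omnibus F rejects. A significant F shows only that the three means are not all equal. It does not by itself establish that each protocol beats the waiting list, or that the added component improves positive affect. A reader who takes the 80% as the chance of detecting g = 0.5 in the comparisons of interest would credit the trial with more power than it has. This matters most for a non-significant TIBP + PA versus TIBP comparison.

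**Working it through.** **Inputs from the article.** Alpha .05, power .80, three equal arms, g = 0.5, f = 0.25, 159 before and 207 after allowance for 30% dropout (Sample size); Tukey after a significant F (Data analyses).

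**1. The plan's own figure.** Omnibus power comes from the noncentral F with 2 and N − 3 degrees of freedom and noncentrality N × f². For f = 0.25 and N = 159, the noncentrality is 159 × 0.0625 = 9.94 and power is 0.805. At N = 156 it is 0.797. So 159 is reproduced exactly, as the omnibus figure for f = 0.25.

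**2. From g to f.** f is the standard deviation of the group means (divisor = number of groups) over the within-group SD.
- Two groups, means 0 and 0.5: f = 0.25. This is where f = d/2 comes from.
- Three groups, means 0, 0.5, 0.5: squared deviations sum to 1/9 + 1/36 + 1/36 = 1/6, so f = √(1/18) = 0.236. This is the maximum for a largest difference of 0.5.
- Three groups, means 0, 0.25, 0.5: f = √(0.125/3) = 0.204. This is the minimum.

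The article states no pattern of means, so these are the bounds. Conversely, f = 0.25 needs a largest difference of 0.25/0.4714 = 0.53 to 0.25/0.4082 = 0.61 SD.

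**3. Omnibus power when the largest difference is 0.5 SD.**

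| f | Noncentrality at N = 159 | Power at N = 159 | N for 80% |
|---|---|---|---|
| 0.236 | 8.83 | 0.75 | 177 |
| 0.204 | 6.63 | 0.62 | 237 |

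**4. Pairwise power at g = 0.5.** The Tukey critical value is q/√2 with 3n − 3 degrees of freedom, and the noncentrality is 0.5 × √(n/2). Three values of n are shown: 48 (69 × 0.7 = 48.3), 53, and 69 (every randomised participant fully informative). The last column requires both protocols to beat the waiting list when both are 0.5 SD better. It comes from simulation with the F-test as a gate.

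| n per arm | Critical value | Noncentrality | Tukey power, one pair | Both protocols beat WL |
|---|---|---|---|---|
| 48 | 2.369 | 2.449 | 0.53 | 0.37 |
| 53 | 2.366 | 2.574 | 0.58 | 0.42 |
| 69 | 2.361 | 2.937 | 0.72 | 0.58 |

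About 83 per arm would be needed for 80% Tukey power per pair at g = 0.5.

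**5. Hypothesis (a) at the cited effects.** For the waitlist comparisons the article cites g = .88 and .93. With 48 per arm, Tukey power per pair is 0.97 and 0.98.

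**6. Hypothesis (c).** The article gives no effect size for TIBP + PA versus TIBP. Assuming g = 0.3 to 0.5, Tukey power with 53 per arm is 0.21 to 0.58.

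**The case against.** The best defence is that the section sizes the trial openly on f = 0.25 for a one-way ANOVA, that 159 is right for that input, and that only a parenthetical is wrong. In the most favourable pattern the slip costs about five points of omnibus power (0.75 against 0.80). All of that stands, and a reader should not infer that the 159 was miscalculated.

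It is also tempting to conclude that the trial is underpowered for its comparison with the waiting list. The article does not support this. It presents 0.5 as deliberately conservative, and at the cited waitlist effects power for (a) is high. The 0.37 to 0.58 for both protocols winning is performance at the conservative value, under a pattern (both active arms 0.5 SD better) that the article does not state.

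The figures at 48 per arm treat dropouts as contributing nothing, although Data analyses plans intention-to-treat mixed models with full information maximum likelihood. That is why the range runs up to 69 per arm. The 0.72 there is an upper bound, because missing outcomes still cost information.

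Finally, a reader might infer that the F-then-Tukey sequence is itself at fault. It is a valid procedure, and the gate costs almost nothing: with means 0, 0.5 and 1.0 and 48 per arm, gated and ungated Tukey power for (c) are 0.533 and 0.534. The article also foresees a review of the methods before analysis.

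None of this makes f = 0.25 equivalent to g = 0.5 in three arms, or makes the 80% a pairwise figure.

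**Conclusion.** The equivalence is wrong as written, and the 80% does not describe the tests that decide (a) and (c). If the largest difference is 0.5 SD, omnibus power at 159 is 0.62 to 0.75. Tukey power per pair at g = 0.5 is 0.53 to 0.72, depending on how much information dropouts contribute. The practical weight falls on (c), where any power figure rests on an assumed effect. Hypotheses (b) and (d) are not superiority contrasts between arms and are not affected in this way.

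The calculations assume equal arms and a common variance. They take no credit for baseline adjustment or repeated measures, because the article gives no correlation. This should be corrected. It threatens neither the type I error nor the validity of the planned tests.

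**What to change.** In Sample size:
- Delete the parenthetical that equates f = 0.25 with g = 0.5.
- State that the 80% is for the omnibus F at f = 0.25, which corresponds to a largest difference of 0.53 to 0.61 SD.
- Report Tukey power per pair at g = 0.5: 0.53 with 48 per arm, 0.58 with 53, and at most 0.72 with 69.
- Say that no separate effect size was assumed for TIBP + PA versus TIBP.

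The cost is rewording and a less favourable power statement. No extra patients are needed.

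Optionally, pre-specify TIBP + PA versus TIBP on the positive affect subscale of the PANAS as a single planned contrast for (c). At an assumed g = 0.5 and 48 per arm, power is 0.68 instead of 0.53. The gain comes from not applying Tukey's adjustment to that contrast, rather than from removing the F-gate, so this is a trade-off to be declared. Any further gain from baseline adjustment depends on an assumed correlation and should be labelled as such.

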**Methods:**

The study is a randomized controlled trial. 207 participants will be randomly assigned to: a)*Transdiagnostic Internet-based protocol (TIBP),* b)*Transdiagnostic Internet-based protocol + positive affect component (TIBP + PA),* or c)a Waiting List control group (WL). Primary outcomes measures will be the BDI-II, the BAI, and the PANAS. Secondary outcomes will include diagnosis-specific measures of the principal disorder. Participants’ treatment acceptance will also be measured. Participants will be assessed at pre-, post-treatment, and 3- and 12- month follow-ups. The data will be analyzed based on the Intention-to-treat principle. Per protocol analyses will also be performed.

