The data obtained with this study can be compared to results obtained in studies with face-to-face transdiagnostic protocols using benchmarking strategies [33]. In addition, the data will also be compared to transdiagnostic protocols applied over the Internet, but without components for up-regulating PA [15, 108–112].

The objective of establishing action strategies to improve access to EBTs should also be taken into consideration, as well as the goal of providing psychological support to all those in need [5]. Undoubtedly, we are witnessing the beginning of a new era in the field of psychological treatments. They have already gone beyond traditional EBTs, and now it is possible to manage these online protocols with good results [53]. The use of technology and the Internet can help to disseminate and increase the access to these interventions.

Finally, we will test the effectiveness of the application of this Internet-based program with minimal support from the clinician, and the acceptability of this online program in patients from a community sample.

We are aware that this study has limitations. One of the most important is the different number of modules in the two protocols. We tried to control this by giving all the participants equal time and allowing them to use the program as much as they like throughout the whole process. However, in order to test the potential additional impact of the positive psychology component, it seemed necessary to compare it to the traditional transdiagnostic protocol. If the new component is found to have any effect, future research should be carried out to show that this effect is not simply due to the larger number of modules in the protocol.

There are further limitations. For example, dropout rates are expected to be high (around 30%) [53, 63]. To minimize this problem, human and ICT support will be provided. In addition, another limitation may be recruitment difficulties, to the extent that people still do not have access to the Internet at home, or they have negative attitudes towards Internet interventions.

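### The 30% dropout allowance multiplies by 1.3 instead of dividing by 0.7, so 207 participants fall short of 80% power at the plan's own dropout rate

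*Protocol article*

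**What the plan says.** The Sample size section of the protocol article fixes the test ("a between-groups one-way ANOVA was assumed for the statistical analyses"), the effect (Cohen's f, where "0.25 represents an effect size of medium magnitude") and the error rates ("considering an alpha of .05 and a statistical power of .80"). From these it derives a total that "contains 159 participants (53 participants per group"). It then expects 30% of participants to be lost during treatment, describes the allowance as covering the largest possible loss, and concludes: "Thus, the required sample size should have 207 participants in all (69 participants per group").

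The Methods part of the Abstract carries the same total: "207 participants will be randomly assigned to" the three arms. The limitations paragraph of the Discussion repeats the rate, in per cent: "dropout rates are expected to be high (around 30"). The formula for the dropout step is not stated.

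**The concern.** A dropout rate is a proportion of the people randomised. To have n analysable participants after a fraction d is lost, one must randomise n/(1 − d). The stated figures instead match n × (1 + d), which adds 30% of the smaller, analysable number. The two agree closely when d is small but not at 30%.

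If this is what was done, the trial is smaller than its own assumptions require. The power of .80 then fails at exactly the dropout rate the allowance was meant to absorb, and a reader of the abstract takes 207 as a number that survives 30% loss when it does not.

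**Working it through.** **Inputs, all from the Sample size section.** k = 3 groups of equal size, f = 0.25, alpha = 0.05, target power 0.80, dropout d = 0.30, analysable total 159 (53 per group), randomised total 207 (69 per group).

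**Step 1: reproduce the base figure.** For a one-way ANOVA, power = P(F′ > F crit), where F′ is noncentral F with 2 and N − 3 degrees of freedom and noncentrality λ = f² × N, and F crit is the upper 5% point of the central F.

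- N = 159: λ = 0.0625 × 159 = 9.94, power 0.805.
- N = 156 (52 per group): power 0.797, just short of 0.80.

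So 159 is the smallest equal-group total that reaches 0.80. The base figure is right.

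**Step 2: reproduce the stated total.**

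- n × (1 + d): 159 × 1.3 = 206.7, rounded up to 207; 53 × 1.3 = 68.9, rounded up to 69. Both match the plan.
- n/(1 − d): 53/0.7 = 75.7, rounded up to 76 per group, or 228 in all (159/0.7 = 227.1). This does not match.

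Rounding does not explain the gap. Starting from 158 or 157 instead of 159, division by 0.7 gives 226 or 225.

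**Step 3: what 207 delivers.**

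- At 30% loss: 207 × 0.7 = 144.9 in all; 69 × 0.7 = 48.3 per group.
- Largest loss that still leaves 159: 1 − 159/207 = 23.2%.
- For comparison, 228 × 0.7 = 159.6, which restores the required number.

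| Loss from 207 | Analysable N | Power at f = 0.25 |
|---|---|---|
| 0% | 207 | 0.902 |
| 20% | 165.6 | 0.822 |
| 23.2% | 159 | 0.805 |
| 25% | 155.3 | 0.795 |
| 30% | 144.9 | 0.764 |

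With whole, equal groups of 48 (N = 144), power is 0.761.

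**Size.** At 30% loss, power is 3.6 to 3.9 points below 0.80. The shortfall is 228 − 207 = 21 participants, or 7 per group.

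**The case against.** Four points can be made in the plan's defence.

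- **Stopping treatment is not the same as losing the outcome.** The plan speaks of loss during treatment. The Data analyses section plans intention-to-treat mixed models with full information maximum likelihood, which keep incomplete cases. People who stop the modules may still complete the post-test, and with no outcome loss 207 gives power of about 0.90. This is a fair reason not to read 0.76 as a forecast for the intention-to-treat analysis. It does not rescue the calculation. The sample size rests on a one-way ANOVA and is inflated explicitly for lost subjects, and the same Data analyses section also plans F-tests on post-test means and a completers-only analysis.
- **The waiting list has no treatment to drop out of.** Purely as an illustration, if only the two treated arms lost 30%, 48 + 48 + 69 = 165 would remain, above 159. The documents make no such assumption: they inflate all three groups equally.
- **The loss of power is small beside the uncertainty in the effect size.** At N = 145, f = 0.26 gives power of 0.798, and the plan says its assumed effect is conservative against the effects it cites. This bears on how serious the error is, not on whether it is one.
- **An article condenses a longer protocol.** This is not an omission that a fuller document could fill. Seventy per cent of 207 is not 159 under any further detail.

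**Conclusion.** The concern holds. The base figure of 159 is correct for its inputs, and the error lies only in the dropout step. At the plan's own 30% loss, 207 randomised leave about 145 analysable participants and power of about 0.76. The stated total keeps 80% power only up to 23.2% loss; the total consistent with 30% loss is 228.

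This rests on the plan's own f = 0.25, equal groups, the omnibus F-test, and dropout meaning that the post-test outcome is not available. It says nothing about power for the pairwise comparisons. The consequence is modest: the chance of missing the assumed effect rises from about 20% to about 24%, with no effect on bias or on the choice of test. It still needs correcting, because it is the trial's headline number and is wrong as written.

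**What to change.** Correct the Sample size section in one of these ways:

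- keep 207 and state that 30% loss leaves about 145 analysable participants (48 per group) with power of about 0.76 at f = 0.25;
- keep 207 and state that it preserves 80% power only up to 23% loss; or
- if 80% power at 30% loss is to be claimed, give 228 (76 per group) and change the Abstract to match.

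Either of the first two costs one sentence, a slightly less favourable claim and no extra patients. The third costs 21 more participants.

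Optionally, adjusting the post-test comparison for the baseline score could recover the lost power without more patients. The documents give no pre-post correlation r, so its value is an assumption. Replacing f² by f²/(1 − r²) at N = 145 gives power of about 0.77 at r = 0.1, 0.78 at r = 0.2, 0.805 at r = 0.3 and 0.88 at r = 0.5. The correction does not depend on this.

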### Study population, recruitment and eligibility criteria

The clinical trial will be conducted in a community sample of patients diagnosed with the aforementioned disorders. Participants will be adult volunteers who contact us because they are interested in the study (personal visits or phone calls to the emotional disorders university clinic, emails, or leaving their data on a website specially prepared for this purpose). Potential participants will be attended to by a psychologist who will describe the study characteristics to them. All the psychologists working on this study will have at least a master’s degree in Clinical Psychology, with experience in the diagnosis, psychological assessment, and application of EBTs for ED.

The psychologist will clarify any doubts, ensure that the participant has read the information about the study, and make sure that s/he has understood the three experimental conditions. People interested in participating will sign an online informed consent and be assessed taking into account all the inclusion criteria. Inclusion and exclusion criteria are shown in Table 1. If the patient fulfills all the study criteria, the researcher will contact an independent researcher to implement randomization. This researcher will be unaware of the characteristics of the study. Randomization will be performed using weighted random allocation [65] in order to take into account the clinical features (different diagnoses) and, thus, obtain a homogeneous distribution in the three experimental conditions. Participants agree to participate before finding out to which treatment they will be allocated. All participants will be free to withdraw from the treatment at any time.

**Table 1 Tab1:** Inclusion and exclusion criteria

Inclusion criteria	Exclusion criteria
Minimal age of 18 years	Suffering from Schizophrenia, bipolar disorder, or alcohol and/or substance dependence disorder
Meeting the DSM-IV diagnostic criteria for ED	High risk of suicide
Ability to understand and read Spanish	Medical disease/condition that prevents the participant from carrying out the psychological treatment
Access to Internet at home and having an email address	Receiving another psychological treatment during the study
Providing online informed consent	An increase and/or change in the pharmacological treatment (in the case of receiving) during the study period

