### Ethics

The study follows the guidelines of the Declaration Helsinki and existing guidelines in Spain and the European Union for the protection of patients in clinical trials. As noted, all participants will be volunteers, and they will sign the online informed consent to form part of the study once it has been explained to them. Participants will have the possibility of withdrawing from the study at any time. The recruitment of participants will be carried out by qualified personnel from a clinical point of view. Participants allocated to the *WL* condition will be offered the opportunity to receive the *TIBP* or the *TIBP + PA* intervention after the waiting time has ended. Based on the literature, no special difficulties are expected. However, any undesired event would not only mean the participant’s departure from the trial, but s/he would also be offered the possibility of receiving psychological care at the Emotional Disorder Clinic in Universitat Jaume I, or of being referred if his/her medical condition required it.

A fundamental aspect in a project of this nature is data protection. To protect information, strategies using personal passwords and data via AES encryption (AES-256; Advanced Encryption Standard) will be used. Personal data will be replaced by codes and data, which must be collected by clinicians (e.g. age, sex, address, and phone), stored separately from other data, and only made available to researchers responsible for the study, always protecting the right to privacy.

The study has been approved by the Ethics Committee of Universitat Jaume I (Castellón, Spain). The trial was registered at clinicalstrial.gov as NCT02578758.

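### Two exclusion criteria and the undesired-event rule can end participation after randomisation, which conflicts with the stated intention-to-treat principle

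*Protocol article*

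**What the plan says.** Three parts of the protocol article bear on this.

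- **Study population, recruitment and eligibility criteria, with Table 1.** Two exclusion criteria are tied to the course of the study: "Receiving another psychological treatment during the study" and "An increase and/or change in the pharmacological treatment (in the case of receiving) during the study period". The text of the same section puts eligibility before allocation: "If the patient fulfills all the study criteria, the researcher will contact an independent researcher to implement randomization".
- **Ethics.** The article states that "any undesired event would not only mean the participant’s departure from the trial"; the participant would also be offered care or referral. The departure is from the trial, not only from the intervention.
- **Data analyses.** "The intention-to-treat principle will be used when analyzing primary and secondary post-treatment data", and likewise for both follow-ups, "using mixed-effect models with full information maximum likelihood estimation". The same section describes an F-test "applied to compare the posttest means for the three experimental conditions", and a separate per-protocol analysis whose selection bias it acknowledges.

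The article nowhere says that participants who meet one of these rules after randomisation are still assessed, and nowhere confines the rules to the per-protocol set.

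**The concern.** A change of medication, a new therapy and an undesired event all happen after allocation and are plausibly linked to how the participant is doing. There are also reasons to expect them to differ by arm:

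- Participants know whether they are on the waiting list. Those who wait have more reason to look for help elsewhere.
- Detection is uneven. The Support section provides weekly calls for the two treatment conditions only, and the worsening alerts and suicide alarms in Adaptation to the web run inside the online program. Undesired events are therefore easier to notice in the active arms.

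If participation ends for such reasons, the people with outcome data are no longer the groups that were randomised. Follow-up is exposed too. The medication criterion refers to the whole study period, and assessment runs to 12 months. Someone who relapses is a likely candidate for a medication change or another therapy, so losing that person would favour the hypothesis that gains are maintained.

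**Working it through.** **Text check.** Randomisation requires that all criteria have been met. Two of the criteria concern what happens while the study runs, so their status is unknown at that moment. They can be applied in full only after randomisation, and intention-to-treat requires that nobody leaves the analysis for such a reason. The statements cannot all be followed literally.

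**Which analyses are exposed.**

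- *Post-test F-test.* It compares post-test means, and no handling of missing values is described for it. Someone who leaves before post-treatment does not contribute.
- *Mixed model, BDI-II and BAI.* Table 2 lists baseline, post-treatment and follow-up. A participant who leaves early still contributes a baseline value, and the estimate is valid under missing at random. However, neither scale is listed between baseline and post-treatment, so worsening that triggers a departure in that interval would not appear in the scores the model uses.
- *Mixed model, PANAS.* As printed, Table 2 lists only post-treatment and post-module assessments. A waiting-list participant who leaves before post-treatment would then contribute no PANAS value. This depends on Table 2 being right; the Abstract promises pre-treatment assessment in general.

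**Size.** The plan has no figure of its own to reproduce here. The only planned number used is the effect size of 0.5 (Sample size), as a scale. The removal rates and D are assumptions.

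Let a fraction p of an arm be removed, with a mean D SD worse than those kept. Then

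full-arm mean = (1 − p) × kept mean + p × (kept mean + D) = kept mean + p × D.

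The mean of those kept therefore looks better than the full arm by p × D, and the waiting-list versus active difference is understated by

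D × (p_WL − p_active).

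- p_WL = 10%, p_active = 5%, D = 0.5: 0.5 × 0.05 = 0.025 SD. A true 0.5 appears as 0.475.
- p_WL = 15%, p_active = 5%, D = 1: 1 × 0.10 = 0.10 SD. A true 0.5 appears as 0.40.
- p_WL = 20%, p_active = 5%, D = 1: 1 × 0.15 = 0.15 SD. A true 0.5 appears as 0.35.
- Rates swapped between arms: the same sizes with opposite sign, so a true 0.5 appears as 0.525 to 0.65.

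**Cross-check with another selection model.** In a simulation with a true difference of 0.5, 10% of the waiting list and 0 to 5% of an active arm were removed, preferentially those with the worst scores. The observed difference was 0.40 to 0.46 when removal correlated 0.5 with outcome, and 0.31 to 0.41 when removal was determined entirely by outcome. It stayed at 0.50 when removal was unrelated to outcome, or was equal and equally selective in both arms. The 0.025 to 0.15 range is thus an illustration and not a bound.

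All these figures compare the means of those kept. They describe the F-test; the mixed model would recover some or all of the shift under missing at random.

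**The case against.** The strongest reply is that Table 1 is a screening list. It is introduced before randomisation, no procedure for later removal is described, and the two items can be read as concurrent or planned co-treatment that participants agree to avoid. The Ethics sentence is about offering care and does not define an analysis set. Data analyses promises intention-to-treat, chooses a model suited to missing data, and has a per-protocol analysis where such deviations would naturally go. A condensed article may also leave post-withdrawal follow-up to the full protocol.

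Much of this stands, and it rules out several stronger readings that a reader might infer:

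- *That collected data are deleted, or that the intention-to-treat analysis is broken.* No section says that data already collected are dropped, and the mixed model can keep them.
- *That the waiting list will be biased by a known amount, such as 0.10 SD.* The rates are assumed and the sign can go either way.
- *That every new prescription on the waiting list triggers exclusion.* The medication item is limited to people already receiving medication, so newly started medication is not clearly covered.
- *That harm is concealed.* Nothing says that undesired events go unreported.

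What does not stand is the appeal to condensation. The point is not that a detail is absent. The article states rules which, taken at their word, work against the analysis principle it also states.

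**Conclusion.** The conflict is real and sits in the wording: two exclusion criteria cannot be settled before randomisation, and the undesired-event rule ends trial participation. Both work against the intention-to-treat statement. Followed literally, they lose outcomes for reasons plausibly related to prognosis and arm. The mixed model limits the damage under missing at random; the post-test F-test, as described, does not.

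The size and direction of any bias cannot be known from the document. The illustrative 0.025 to 0.15 SD is 5% to 30% of the planned 0.5 (0.025 / 0.5 and 0.15 / 0.5). It assumes 10 to 20% removed from one arm, 5% from the other, and removed participants 0.5 to 1 SD worse than those kept. It understates benefit if the waiting list loses more and overstates it if the active arms do. There is no bias if removal is unrelated to outcome, or is equal and equally selective across arms. The point deserves correction because outcomes that are never collected cannot be recovered at analysis.

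**What to change.** Reconcile Table 1 and its section, the Ethics sentence and Data analyses by stating that:

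- eligibility is fixed at randomisation;
- everyone randomised stays in the intention-to-treat set, and post-treatment and follow-up outcomes are sought from them regardless of medication changes, other psychological treatment or undesired events, subject to consent;
- these events are recorded by arm and lead to exclusion only in the per-protocol or sensitivity analyses.

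Whether the intervention stops after such an event, and how the event is handled clinically, is for the investigators and is not judged here.

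The cost is a few sentences and a few more online questionnaires. The one downside is that the intention-to-treat estimate will include the effect of any co-treatment, which is what that principle implies.
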